## 9. METHODS

### 9.1 Study algorithms

#### 9.1.1 TME-study

[figure not shown]

**Fig 1.** Study layout for impacted third molar extraction (TME) participants. The general timelines of the impacted third molar extraction (TME) study. Information day (green bar) where participants are informed about the study. The day of surgery (red), the follow-up phone call (yellow; 2 weeks  $\pm$  3 days] after TME), the first examination day (Day 1; dark blue; 4 weeks  $\pm$  3 days]) and the second examination day (Day 2; blue; exactly 7 days after Day 1).

[figure not shown]

**Fig 2.** Test-algorithm Day 1/2 for TME-participants and Day 2/4 for BI-participants with superimposed naloxone plasma-concentration curves. Median plasma-concentration (red) with 95% CI (dashed black lines) during a three-step target-controlled-infusion (TCI). Naloxone is given at step one with 0.25 mg/kg, step two 0.75 mg/kg and step three 2.25 mg/kg. Yellow timeline columns represent ratings with Clinical Opiate Withdrawal Scale (COWS) and blue columns indicate sensory testing (pain during rest, movement and 100 kPa pressure; pressure algometry; secondary hyperalgesia area). **BL** = baseline assessments (-20" to -8"; please, observe for BI-participants baseline assessments are made - 2hrs 20"

to – 2hrs 8" before start of TCI); **S1** = step one assessments (15" to 25"); **S2** = step two assessments (39" to 49"); **S3** = step three assessments (65" to 75").

At the follow-up phone call 2 weeks ( $\pm$  3 days) after surgery any questions the participant may have regarding the study will be discussed. The post-surgical pain intensity and signs of post-surgical complications will be penetrated (swelling, pain, fever, malaise, excessive lymph-node swelling).

The study drug (naloxone or placebo) will be given in a randomized fashion on the examination days, Day 1 and Day 2. Day 1 takes place 4 weeks ( $\pm$  3 days) after surgery. Day 1 and Day 2, separated by exactly 7 days, are at Department of Neuroanaesthesia 3042, Rigshospitalet (Fig. 1). Procedures on Day 1 and Day 2 will be performed by a physician and a research-nurse.

The agenda for the examination days are:

#### 9.1.2.1.1 Day 1/Day 2

- Assessment of inclusion and exclusion criteria
- The participant gives his informed consent (only Day 1)
- The participant fills out the Hospital Anxiety and Depression Scale (HADS; only Day 1)
- The participant fills out the Pain Catastrophizing Scale (PCS; only Day 1)
- The examiner fills out the Clinical Opiate Withdrawal Scale (COWS)
- Brief medical examination (only Day 1):
  - Medical history
  - Auscultation of heart and lungs
  - Blood pressure and heart rate
  - Routine palpation of lymphatic nodes in the submandibular regions, the supraclavicular fossae and the axillae.
  - Assessment of deep tendon reflexes
- Urine-sample to test for opioids (sample is discarded just after the analysis).
- Randomization (consecutively by pre-specified randomization)
- Monitoring with three-lead ECG and measurements of pulse oximetry, blood pressure and respiratory rate is started.
- Baseline assessments are performed at **time – 20" to – 8"** (Fig. 2):
  - Reaction time assessed as Online Reaction Time.
  - Pain rating (0-10, NRS) at rest in the supine position.
  - Pain rating (0-10, NRS) during a standardized mastication procedure.
  - Pain rating (0-10, NRS) during pressure-algometry applied perpendicularly at the mandibular skin sites overlying the surgical area and the contralateral mirror-site.
  - Secondary hyperalgesia/allodynia at surgical site and contralateral mirror-site at the mandibular skin sites overlying the surgical area and the contralateral mirror-site.
- **Time 0" to 25": First** step target-controlled-infusion (TCI; including a bolus dose) of naloxone/placebo infusion (**Fig. 2**)
- **Time 13" to 15":** The examiner assesses COWS-rating

- **Time 15'' to 25''**: Identical assessments as made at baseline are repeated
- **Time 25'' to 50''**: **Second** step TCI (including a bolus dose) of naloxone/placebo infusion (**Fig. 2**)
- **Time 37'' to 39''**: The examiner assesses COWS-rating
- **Time 39'' to 49''**: Identical assessments as made at baseline are repeated
- **Time 50'' to 75''**: **Third** step TCI (including a bolus dose) of naloxone/placebo infusion (**Fig. 2**)
- **Time 63'' to 65''**: The examiner assesses COWS-rating
- **Time 65'' to 75''**: Identical assessments as made at baseline are repeated
- **Time 75''**: End of naloxone/placebo infusion
- Monitoring data are continuously registered and documented
- Potential side-effects are continuously registered and documented
- **Time 75'' – 180''**: observation period where the participant is allowed to drink, eat and begin to ambulate. Monitoring is continued until 100''
- **Time 180''**: the participant is discharged

The participants will be contacted by phone [name] the day after each examination day to check up on potential side effects. The examiner [name] will be on call on mobile at the request of the participant for 24 hrs after each examination day.

#### 9.1.2 BI-study

Participants are screened during a separate day (Day 0; 1½ hrs; Fig. 3): a burn injury is induced and secondary hyperalgesia areas are assessed. The boundaries of 25% and 75% quartiles for secondary hyperalgesia areas (22 cm^2 [low-sensitizers] and 37 cm^2 [high-sensitizers], respectively [Ringsted TK, et al. (2015) J Neurosci Methods 256: 74-81]) are used to allocate participants into low-sensitizers (areas ≤ 22 cm^2) and high-sensitizers (areas ≥ 37 cm^2). Data from the 80 participants are used to determine contemporary and probably more accurate boundaries of 25% and 75% quartiles for secondary hyperalgesia areas! Only low-sensitizers and high-sensitizers continue in the study, the remaining participants are excluded.

Day 1 and Day 3 are identical testing days with induction of BI's and sensory assessments (Figs. 3-4). Day 2 and Day 4 are identical TCI-testing days (Figs. 3-4), with participants randomized and allocated to receive either placebo or naloxone.

##### 9.1.2.1 Screening day: Day 0 (Fig. 3).

- The participants have been instructed to use a hair trimmer in the test areas on both lower legs, two days before each study session.
- Assessment of inclusion and exclusion criteria
- The participant gives his informed consent
- The participant fills out the Hospital Anxiety and Depression Scale (HADS)
- The participant fills out the Pain Catastrophizing Scale (PCS)

- The examiner fills out the Clinical Opiate Withdrawal Scale (COWS)
- Brief medical examination:
  - Medical history
  - Auscultation of heart and lungs
  - Blood pressure and heart rate
  - Routine palpation of lymphatic nodes in the submandibular regions, the supraclavicular fossae and the axillae.
  - Assessment of deep tendon reflexes
- Urine-sample to test for opioids (sample is discarded just after the analysis).
- **Baseline assessments** (all sensory assessments are made at the **left** leg):
  - The corners of the BI-area is outlined by a marker on the medial aspect of the lower leg with the upper margin 11 cm below the medial meniscus and the anterior border 7 cm behind the anterior margin of the tibia.
  - The secondary hyperalgesia area is determined using a “weighted-pin” stimulator (cf. 9.2.5.2). A **green** marker is used to indicate the transition zone.
  - Pin-prick pain thresholds (PPTs) in the primary BI-area and in the secondary hyperalgesia area are assessed by “weighted-pin” stimulators (cf. 9.2.7) .
- **Burn injury induction:**
  - A first-degree BI is induced by a computerized contact thermode (MSA Thermal Stimulator, Somedic AB, Hörby, Sweden; 5.0 x 2.5 cm^2; 47.0°C, 420 s) applied with gentle pressure at the pre-specified area.
  - Pain intensity is assessed by NRS (0-10) during the BI-induction (cf. 9.2.4.2).
- **Post-injury assessments:**
  - **Time 1 hr 7"** after start of induction, secondary hyperalgesia areas are demarcated (cf. 9.2.5.2), using a **red** marker.
  - PPT's are assessed, as described above.
  - The demarcations of hyperalgesia areas are transferred to clear acetate sheets.
  - The sheets are scanned, and calculations of the octagon areas (total area minus the area of thermode) are by a computer program (Canvas 12.0, ACD International Systems, Victoria, Canada).
  - The participants are allocated to low-sensitizers and high-sensitizers

#### 9.1.2.2 Burn injury days: Day 1 (right leg)/Day 3 (left leg; [Figs. 3 and 4]):

- The participants have been instructed to use a hair trimmer in the test areas on both lower legs, two days before each study session.
- It is verified that the participant belongs to either the low-sensitizer group or the high-sensitizer group.
- Urine-sample to test for opioids (sample is discarded just after the analysis).
- **Baseline assessments**, as previously described (Day 0; Fig. 4).

- **Burn injury induction**, as previously described (Day 0; Fig. 4).
  - **Post-injury assessments**, as previously described (Day 0; Fig. 4). However, an additional 2 hrs post-injury assessment is made at **time 2 hrs 7"** after induction of the burn injury (cf. 9.2.5.2), using a **green** marker.

[figure not shown]

**Fig 3.** General study layout for the burn injury (BI) study. BIs are induced Day 0, Day 1 and Day 3. Day 0 is a screening day, including high-sensitizers (large secondary hyperalgesia areas; 75% quartile) and low-sensitizers (small secondary hyperalgesia areas 25% quartile). Day 1 and Day 3 include induction of BIs in high- and low-sensitizers. Target-controlled-infusion (TCI) days are Day 2 and Day 4, with randomized allocation between placebo and naloxone. The time line between Day 1 and Day 2, and, Day 3 and Day 4, is 7 days. The timeline between Day 3 and Day 0 is 8 weeks or more.

[figure not shown]

**Fig 4.** Study layout for the burn injury (BI) study. Day 1/Day 3 includes induction of BI (mild thermal injury; 47C°, 7") with baseline assessments (green rectangle), burn injury (red) and post-injury assessments (blue). Day 2/Day 4 include a pre-drug assessment (blue; post-injury 165 hrs), drug-infusions (naloxone or placebo; 167-168 hrs) and assessments during target-controlled-infusion ([TCI]; light green). The estimated plasma concentrations are superimposed in dashed red line. Roman numerals indicate the three TCI-steps. Stars indicate assessments of pin-prick pain thresholds (red), and secondary hyperalgesia areas (green star).

#### 9.1.2.3 TCI-days: Day 2 (right leg)/Day 4 (left leg; [Figs. 3 and 4]):

The study drug, naloxone will be given by a TCI-regimen at the Multidisciplinary Pain Center 7612 or Department of Neuroanaesthesia 3042, both at Rigshospitalet. Procedures on the study day will be performed by a physician and a research-nurse.

- The participants have been instructed to use a hair trimmer in the test areas on both lower legs, two days before each study session.

- The examiner fills out the Clinical Opiate Withdrawal Scale (COWS).
  - Urine-sample to test for opioids (sample is discarded just after the analysis).
  - Online Reaction Time is measured, as previously described (Day 0).
  - Randomization (consecutively by pre-specified randomization)
  - Monitoring with three-lead ECG and measurements of pulse oximetry, blood pressure and respiratory rate is started.
- 
- **Time 165 hrs** after induction of the BI Baseline, **Baseline assessments**, as previously described (Day 0), is performed (Fig. 4). A **blue** marker is used to demarcate the secondary hyperalgesia area.
  - **Time 167 hrs 20" to 167 hrs 45": First** step target-controlled-infusion (TCI; including a bolus dose) of naloxone/placebo infusion (Fig. 4).
  - **Time 167 hrs 33" to 167 hrs 35":** The examiner assesses COWS-rating.
  - **Time 167 hrs 35" to 167 hrs 45":** Identical assessments as made at baseline are repeated. A **red** marker is used to demarcate the secondary hyperalgesia area.
  - **Time 167 hrs 45" to 168 hrs 10": Second** step TCI (including a bolus dose) of naloxone/placebo infusion (Fig. 4).
  - **Time 167 hrs 57" to 59":** The examiner assesses COWS-rating.
  - **Time 167 hrs 59" to 168 hrs 09":** Identical assessments as made at baseline are repeated. A **green** marker is used to demarcate the secondary hyperalgesia area.
  - **Time 168 hrs 10" to 168 hrs 35": Third** step TCI (including a bolus dose) of naloxone/placebo infusion (Fig. 4).
  - **Time 168 hrs 23" to 168 hrs 25":** The examiner assesses COWS-rating.
  - **Time 168 hrs 25" to 168 hrs 35":** Identical assessments as made at baseline are repeated. A **black** marker is used to demarcate the secondary hyperalgesia area.
  - **Time 168 hrs 35":** End of naloxone/placebo infusion.
  - Monitoring data are continuously registered and documented.
  - Potential side-effects are continuously registered and documented
  - **Time 168 hrs 35" to 170 hrs 20":** observation period where the participant is allowed to drink, eat and begin to ambulate. Monitoring is continued until **169 hrs 00"**. The peripheral i.v. cannula is removed at **169 hrs 00"**.
  - **Time 170 hrs 20":** the participant is discharged

The participants will be contacted by phone [name] the day after each examination day to check up on potential side effects. The examiner [name] will be on call on mobile at the request of the participant for 24 hrs after each examination day.

## 9.2 Clinical assessments (TME-participants and BI-participants)

### 9.2.1 Psychometric evaluation

On Day 1 for TME-participants and Day 0 for BI-participants, a psychometric evaluation with HADS and PCS will be performed. These evaluations are made since anxiety, depressive thoughts and catastrophizing behavior may predispose to increased or even exaggerated pain sensitivity.

The Hospital Anxiety and Depression Scale (HADS) is used to assess anxiety and signs of depression. Based on 14 questions about the subject's status in the previous week, HADS measures agitation/anxiety and depression via two subscales (each containing seven questions). Participants have to answer each question on a scale of 0 to 3. The two subscales are summed separately. The maximum score of each subscale is 21 points and a score of 11 or more points suggests that the participant might be suffering from anxiety or depression. In case of score  $\geq 11$  points in the depression subscale of the HADS, a physician will decide if there are clinical signs of depression. If there are signs of depression, this diagnosis will be told to the participant. The participant will be informed that the diagnosis of depression is based on clinical assessments – the HADS scale can be included in the diagnostic procedure. If it is the participants wish, he should visit his general practitioner for diagnosis and eventual treatment. Participants with significant signs of depression will be excluded from the study.

The Pain Catastrophizing Scale (PCS) consists of 13 questions divided into three sections: rumination, exaggeration and helplessness. The questions are answered in accordance to a scale of 0 to 4. There is evidence of catastrophizing thoughts at a total score  $> 30$  points.

#### 9.2.2 Evaluation of opioid withdrawal (BI-participants Day 0 not included)

The Clinical Opiate Withdrawal Scale (COWS) is an examiner-based scale evaluating signs of opioid-withdrawal. Grading of symptoms, i.e. heart rate changes, sweating, restlessness, pupil size, bone or joint aches, running nose or tearing, nausea, vomiting, diarrhea, tremor, yawning, anxiety or irritability and “goose-flesh”, are made in 11 categories. COWS-scores are divided into: 5-12 = mild; 13-24 = moderate; 25-36 = moderately severe ; $> 36$  = severe withdrawal reactions.

#### 9.2.3 Reaction time

Online Reaction Time is measured using <http://getyourwebsiteherecom/jswb/rttest01.htm>. This computer-application shows a red-green traffic light. Participants are instructed to press the button when the light changes from red to green. Three measurements are used and the median value is used as a representative estimate of reaction time.

#### 9.2.4 Pain assessments

##### 9.2.4.1 TME-participants

Pain assessments are performed in three different situations:

- \* Pain rating (0-10, NRS) at rest in the supine position
- \* Pain rating (0-10, NRS) during a standardized mastication procedure. Pain is evaluated by asking the participant to chew a preparedD chewing gum (between the upper and lower, first molar of the surgical side during 30 seconds at a cycles of 40 Hz controlled by a iPhone-driven metronome (app. Steinway

---

D

Musical Instruments 1.1.4). Volunteers will be instructed that each chewing cycle ends when the upper and lower teeth clench and this time-point should be synchronized with the metronome. Volunteers will then rate the maximum pain intensity evoked by the task.

The sugar-free chewing gum (V6; Mondelez, Denmark) is prepared by the participant by chewing on the gum in 2" immediately at the start of the examination day. The gum is thereafter kept in a plastic container and re-used by the participant during the mastication procedure.

\* Pain rating (0-10, NRS) during a pressure stimulus (100 kPa) applied perpendicularly at the mandibular skin sites overlying the surgical area and the contralateral mirror-site, using a pressure algometer (Somedic AB, Hörby, Sweden) with a 1-cm^2 felt-tipped probe, directed at the point of maximum pain. During the measurement, the investigator will stabilize the lower jaw by sliding the gloved, index finger along the internal side of the body of the mandible, while applying lateral indirect pressure (100 kPa), externally to the relaxed masseter muscle. The participants rate the maximal, experienced pain intensity (0-10 NRS).

#### *9.2.4.2 BI-participants*

Pain ratings is assessed by NRS (0-10) at 0',30',60',120',180',240',300' and 360' after start of BI-induction.

#### *9.2.5 Secondary hyperalgesia/allodynia*

##### *9.2.5.1 TME-participants*

Secondary hyperalgesia/allodynia at surgical site and contralateral mirror-site at the mandibular skin sites overlying the surgical area and the contralateral mirror-site using a nylon monofilament (nominal value 4.93 [bending force: mean + SD = 69 + 14 mN]).

##### *9.2.5.2 BI-participants*

The secondary hyperalgesia area is determined using a "weighted-pin" stimulator (PinPrick stimulators, MRC Systems GmbH, Heidelberg, Germany; 128 mN [2,606 kPa]). The borders of the areas are assessed by stimulating along eight symmetrical lines, converging towards the center of the BI. The stimulation path starts at least 12 cm outside the borders of the BI-area. The participants are instructed to report, with their eyes closed, when the perception of the stimulus changes from an innocuous pin-prick to a stinging, smarting and unpleasant sensation, and the position is indicated by a marker. Normally, a secondary hyperalgesia area is **not** present in uninjured skin. If the participant anyhow experiences a transition zone, the participant is told to memorize the perceptual quality of the transition zone, and compare this with the perceptual quality during demarcation of secondary hyperalgesia following the burn injury (as a general rule there are clear perceptual qualitative and quantitative differences between hyperalgesia in an un-injured vis-à-vis an injured area. If the participant is unable to tell the difference, the participant is excluded from the study.

#### *9.2.6 Pressure pain threshold (TME-participants)*

Pressure pain threshold (PPT) will be assessed using an electronic pressure algometer (Algometer, Somedic AB, Sweden). The pressure algometer employs a 1-cm^2 circular probe, which is applied manually, perpendicularly to the skin with increasing pressure at a rate of 1-2 kPa/s. The assessment area will include the point of maximum pain. PPT assessments will be performed at baseline (-20 min to -8 min; Fig. 2) and during infusions (15 min to 25 min; 39 min to 49 min; 65 min to 75 min) at the surgical site and at the mirror-site in the contralateral groin. The participants interrupt the stimulation by pushing a button when the pressure becomes painful, and the investigator then stops the stimulation. The cut-off value is 350 kPa. Values exceeding the cut-off are designated 351 kPa.

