In regard to the risk of development of a sustained pain state after the naloxone administration in individuals after TME, we consider it highly unlikely. *First*, naloxone does not affect the production of endogenous opioids, but only acts as a short-acting reversible antagonist of opioids. *Second*, in adults the distribution half-life ( $T_{1/2\alpha}$ ) of naloxone is 40 to 70 seconds [26], and the elimination ( $T_{1/2\beta}$ ) half-life, 54 to 64 min [26] [27]. Naloxone has not any known long-acting metabolites and thus there are no pharmacokinetic reasons for a prolonged reversal of endogenous opioids. *Third*, in studies with rodents, administration of naltrexone or naloxone has caused transient episodes of hypersensitivity with duration of 60 to 90 min [9]. Repeated administration of naltrexone, over the course of months, has confirmed full reversibility of the hypersensitivity episodes. *Fourth*, in our recent patient-study with high dose naloxone (H-2-2012-174) in 4 of 12 individuals responding to naloxone, very short lasting changes in hypersensitivity were seen [12]. Thus it is our strong belief that the likelihood of development of significant or serious adverse effects, including sustained pain, is minimal in this study.

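### The TME pressure-threshold ramp in section 9.2.6 can use most or all of the 10-minute test window and, at its slow end, overrun it; the same section names the groin as the control site for a jaw operation

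*Protocol*

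**What the plan says.** Section 9.2.6 describes the pressure pain threshold for TME-participants. The probe is "applied manually, perpendicularly to the skin with increasing pressure at a rate of 1-2 kPa/s". On the upper limit it says "The cut-off value is 350 kPa. Values exceeding the cut-off are designated 351 kPa". Readings are taken at baseline and "during infusions (15 min to 25 min; 39 min to 49 min; 65 min to 75 min", and the two sites are "at the surgical site and at the mirror-site in the contralateral groin".

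The same windows hold other tests. The section 9.1.1 agenda lists, in this order, reaction time, pain at rest, pain on chewing, pain under pressure algometry and secondary hyperalgesia/allodynia. It gives the pressure-pain stimulus as "applied perpendicularly at the mandibular skin sites overlying the surgical area and the contralateral mirror-site". The agenda has no separate line for the pressure threshold, but the Fig. 2 legend lists pressure algometry in addition to the 100 kPa pain rating.

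On dosing, the Fig. 2 legend says "Naloxone is given at step one with 0.25 mg/kg, step two 0.75 mg/kg and step three 2.25 mg/kg". Sections 9.1.1 and 11.1 start step 2 at 25 min and step 3 at 50 min, each with a bolus, and end the infusion at 75 min.

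Section 13.2.1 uses the pressure pain threshold as a fixed factor in a mixed model for the primary outcome. Section 3.2.1 does not list it as a secondary outcome.

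**The concern.** A stepped infusion is informative only if each reading belongs to the step under which it is filed. The windows have almost no slack: the first closes exactly when the step 2 bolus starts, the second closes one minute before the step 3 bolus, and the third closes when the infusion ends. A slow ramp at two sites, added to five other kinds of test, may not fit. Ramp time is proportional to the threshold, so any overrun is longest in participants with the highest thresholds. The timing error is therefore tied to the measured value.

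The site wording is a separate matter. A threshold taken at the groin cannot act as the within-person control for one taken at the mandible.

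**Working it through.** **Inputs.** Ramp 1 to 2 kPa/s, cut-off 350 kPa, two sites (9.2.6). Windows 15-25, 39-49 and 65-75 min, so 600 s each (9.2.6, 9.1.1). Chewing 30 s (9.2.4.1). Expected baseline pressure-evoked pain at 100 kPa: mean 4, SD 2 NRS units (13.1.1). Bolus and infusion doses (11.1). One ramp per site, since no repeats are stated.

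**The plan's own dose figures.** Bolus plus infusion: 0.02 + 0.23 = 0.25; 0.06 + 0.69 = 0.75; 0.18 + 2.07 = 2.25 mg/kg. The total is 3.25 mg/kg, as stated, and each step is three times the one before. The predicted median plasma levels of 344, 1,059 and 3,196 ng/ml have ratios of 3.08 and 3.02.

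**Time for thresholds alone** = (sum of the two thresholds) / ramp rate.

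| Case | 1 kPa/s | 2 kPa/s |
|---|---|---|
| Both sites at cut-off (350 + 350 kPa) | 700 s = 11.67 min | 350 s = 5.83 min |
| Surgical side 100 kPa, other side at cut-off (450 kPa) | 450 s = 7.5 min | 225 s = 3.75 min |

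Break-even rate for two full ramps: 700 / 600 = 1.17 kPa/s. Of the permitted range, only 1.00 to 1.17 kPa/s fails on thresholds alone. At 1 kPa/s, failure needs thresholds summing to more than 600 kPa.

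**Where the worst overrun falls** (1 kPa/s, both sites at cut-off, thresholds started when the window opens):
- Step 1: 15 + 11.67 = 26.67 min, which is 1.67 min into step 2. By then the whole 0.06 mg/kg bolus and 40 s of infusion 2 have been given: 0.06 + 0.69 × (40 / 1,440) = 0.079 mg/kg, or 32% of the step 1 dose.
- Step 2: 39 + 11.67 = 50.67 min, which is 0.67 min into the step 3 bolus.
- Step 3: 65 + 11.67 = 76.67 min, which is 1.67 min after the infusion ends.

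**Adding other tests.** With 30 s of chewing, the cut-off case takes 12.17 min at 1 kPa/s and 6.33 min at 2 kPa/s. Section 9.2.4.1 gives no rate for the 100 kPa stimulus. If it uses the same ramp at both sites (an assumption), it adds 200 s or 100 s. The totals are then:
- Cut-off case: 15.5 or 8.0 min.
- 100/350 kPa case: (450 + 30 + 200) / 60 = 11.33 min or (225 + 30 + 100) / 60 = 5.92 min.

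Reaction time, resting pain and monofilament testing come on top, and the protocol gives no durations for them.

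**Site.** Sections 3.2.1, 9.1.1, 9.2.4.1 and 9.2.5.1 all place the contralateral site on the mandible. Only section 9.2.6 names the groin.

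**The case against.** The best reply is that two full ramps at the slowest rate are a corner case. The ramp stops when pressure becomes painful. A mean rating of 4 at 100 kPa implies that the typical surgical-side threshold is below 100 kPa, and at 2 kPa/s even two cut-offs fit. No typical-case overrun can be demonstrated, because several durations are not stated. This stands, and it limits the claim to a window that can be overrun and is tight.

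A reader might infer that the primary comparison is contaminated. The documents do not support that. The primary outcome is the NRS composite, and the agenda lists its three ratings ahead of area mapping. If thresholds come last, a late threshold leaves those ratings untouched. What remains is that the order is not declared binding and the agenda never places the threshold test.

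A reader might also infer that a late step 3 reading is taken after the drug has largely gone, because section 1.1 says the distribution half-life of "naloxone is 40 to 70 seconds". The same sentence gives an elimination half-life of 54 to 64 min. Over 100 s the fall would be 63 to 82% if distribution governed (1 − 2^(−100/70) to 1 − 2^(−100/40)), but only about 2% if elimination did (1 − 2^(−1.67/64) to 1 − 2^(−1.67/54)). The documents do not say which dominates at 75 min, so no loss of effect can be claimed.

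Finally, the groin wording is probably carried over from the groin-hernia study mentioned in section 1.1 (an inference), and most readers would see what was meant. It is still an operative instruction in the methods section.

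**Conclusion.** Both parts hold, at moderate weight. The stated rate, cut-off, number of sites and window length are compatible only over part of their stated ranges. Thresholds to cut-off use 58 to 117% of the window (350/600 to 700/600). In the 100/350 kPa case they use 38 to 75% (225/600 to 450/600), before any other test. That case assumes a surgical-side threshold of 100 kPa and the other side at the cut-off.

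The consequence is that some thresholds may be filed under a step at which they were not taken, more often in people with high thresholds. The analysis exposed is the section 13.2.1 mixed model, in which the threshold is a fixed factor. An effect on the primary composite is not shown. The groin wording is a plain contradiction and needs no assumption.

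**What to change.** - In 9.2.6, reconcile ramp rate, cut-off and window by setting a faster ramp that leaves room for the other tests. As an example, 10 kPa/s takes at most 2 × 35 = 70 s for both sites. If the 100 kPa stimuli use it too, they take 2 × 10 = 20 s, so with 30 s of chewing the timed tests need 120 s and 480 s remain.
- In 9.2.6, replace the groin with the contralateral mandibular mirror-site.
- In 9.1.1, list the threshold test and state the order: the three primary pain ratings first, pressure threshold last.
- Do not discard thresholds still running at the window limit, since that would remove the highest values selectively. If a ramp is cut short, record it as censored at the pressure reached.

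The cost is protocol wording and an algometer setting. A faster ramp adds some reaction-time overshoot: for an assumed 0.5 s delay, about 5 kPa at 10 kPa/s against 0.5 to 1 kPa at the present rate. It should be similar on both study days, so it should largely cancel in the naloxone-placebo comparison.
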